### Randomization

2.4

Patients who met the inclusion criteria will be randomly assigned to blank control group and LPGBD group in the ratio of 1:1. Measures to Reduce the Risk of Bias Concealed randomization prevents selection bias. The random allocation sequence listing was generated by a statistician who will not participate in the clinical study using SAS v9.4 (SAS Institute, Cary, NC).5-10 minutes before treatment, the doctor will inform the patient about the randomization procedure, telephone number and name; then, the doctor will be informed of the random number of patients and the treatment group. The randomization information will be concealed until the end of the trial.

### Blinding

2.5

Due to the nature of TCM, doctors and patients will know the grouping information. However, principal investigator, statisticians, and outcome evaluators will be blinded to group allocation.

### Researchers

2.6

Five principal investigator with TCM background will be responsible for data collection. The supervisors and analysts who do not know the regulatory data will monitor the entire experiment. The principal investigator, outcome evaluators, and statisticians will be strictly trained before trial.

### Recruitment

2.7

Patients will be recruited in the gastroenterology outpatient clinics of the First Affiliated Hospital of Guizhou University of TCM. The poster will briefly describe the trial and provide treatment details, as well as contact information. If a potential participant is interested in taking part, they can directly contact the study team. We will provide potential participants with detailed information about benefits and possible risks of the trial. If they decide to participate, they will be asked to sign written informed consent. If a participant withdraws from the trial, the reason for the withdrawal will be recorded. In order to improve the compliance of patients, we will strengthen doctor-patient communication and timely health education for patients.

### Patient safety

2.8

Potential adverse events associated TCM include rash, skin allergy and liver and kidney function damage. Clinicians record the occurrence of any adverse events and the intervention will be stopped immediately. The independent safety supervision committee composed of 3 experts from different fields in the First Affiliated Hospital of Guizhou University of TCM has the right to terminate the study.

## Interventions

3

### The blank control group

3.1

Subjects in the blank control group will receive conventional treatment: Pinaverium Bromide Tablets (50 mg), orally 3 times daily for 12weeks; Bifidobacterium triple viable capsule (420 mg), orally twice times daily for 12weeks.

### The LPGBD group

3.2

Subjects in the LPGBD group will be given LPGBD, based on the conventional treatment in the blank control group. The herbal formula of LPGBD comprises the following TCM: fried Atractylodes macrocephala 15 g, Poria cocos 10 g, tangerine peel 6G, Rhizoma Pinelliae 10 g, Shenqu 10 g, malt 15 g, roasted licorice 6G, Astragalus 20 g, Paeonia Alba 10 g. The medicinal materials were decocted twice at 100 °C under a normal pressure, each for 40 minutes. Each decoction (150 ml) should be taken twice a day.

### The course of treatment

3.3

The duration of treatment was 12 weeks.

### Combined treatment regulations

3.4

During the trial, Participants are prohibited from taking any other TCM, western medicine or therapeutic measures (such as acupuncture, cupping, and massage). If a concomitant intervention is used, the name, dosage, and frequency of the accompanying interventions should be recorded in detail.

## Outcome measures

4

### Primary outcome

4.1

Disease outcomes include cure, significant effect, effective, and ineffective. The main outcome will be the total clinical effective rate of the 2 groups after treatment (week 12), that is, that is, the sum of cure rate, apparent efficiency and effective. Outcome indicators will be collected at the 12th week.

### Secondary outcomes

4.2

(1)IBS clinical symptom scores: abdominal pain, diarrhea, abdominal distension will be scored as follows: 0, none;2, light;4, moderate; 6, heavy. IBS clinical symptom scores will be measured on week 0, 4,8, 12.(2)IBS-Quality of life (IBS-QOL): IBS-QOL consists of 8 domains: dysphoria, interference with activity, body image, health worry, food avoidance, social reaction, sexual function and impact on relations. The IBS-QOL score ranged from 0 to 100 points and a higher score indicated a better QOL. IBS-QOL will be measured on week 0, 4,8, 12.(3)IBS-Severity Scoring System (IBS-SSS): The IBS-SSS score ranged from 0 to 500 points and a higher score indicated a worse SSS. The IBS-SSS are scored as follows: mild, ≤175 points; moderate severity, >175 points and ≤300 points; severe, >300 points. IBS-SSS will be measured on week 0, 4,8, 12.(4)Hamilton Rating Scale for Anxiety (HAMA): HAMA are scored as follows: normal, <7 points; suspected anxiety, 7 to 14 points; definite anxiety, 14 to 21 points; obvious anxiety, 21 to 29 points; serious anxiety, ≥29 points. HAMA will be measured on week 0, 4,8, 12.(5)Hamilton Depression Scale: HAMA are scored as follows: normal, <8 points; suspected depression, 8-20 points; definite depression, 20 to 35 points; severe depression, >35 points. Hamilton Rating Scale for Depression will be measured on week 0, 4,8, 12.(6)Bristol Stool Form Scale: Bristol Stool Form Scale will be measured on week 0, 4,8, 12.

### Safety outcomes

4.3

Safety results will include echocardiogram, blood tests (including routine blood tests, liver function tests and kidneys function tests), urine routine tests and stool routine tests. All outcomes be measured on week 0, 4,8, 12. If an adverse event occurs, the investigator will record the details (including symptoms, time of occurrence, duration, examination, and results) in the form of a case record form (CRF). Serious adverse reactions will be reported to the ethics committee of the First Affiliated Hospital of Guizhou University of TCM, and relevant rescue procedures will be started immediately.

### Data management

4.4

Test data need to be recorded in paper-based and electronic CRF. An independent data-monitoring committee reviewed the data every 3 months. During the trial, only data managers and principal investigators will have access to the electronic CRF. At the end of the trial, the database will be locked by the data management team, after which the principal investigators cannot modify the data. Paper and electronic documents will be kept for at least 5 years. If readers and reviewers have any questions, they can contact the appropriate author to obtain the original content data.

## Ethics

5

This study has been approved by the ethics committee of the First Affiliated Hospital of Guizhou University of TCM (ethical approval number: YE2020-126-11) and registered in the China clinical trial registration center on November 3, 2020. The trial strictly followed the Helsinki Declaration (2000 EDITION). Only patients with informed consent can participate in the trial.

## Dissemination

6

The results of the study will be communicated to healthcare professionals, participants and the public through peer-reviewed publications, scientific conferences. Moreover, the data of this study can be obtained from corresponding authors according to reasonable requirements.

## Confidentiality

7

All personal information of the participants will be kept strictly confidential and the anonymized individual patient data will be shared on request.

## Ancillary and post-trial care

8

In case of direct injury related to this study, corresponding medical and nursing care can be obtained. Emergency contact number will be Provided for each subject so that they can contact the researcher whenever they have any questions or questions.

## Statistical analysis

9

The clinical results will be analyzed by SPSS 22.0 statistical software (IBM SPSS statistics, IBM Corp, Somers, NY). In this study, the intention-to-treat analysis and per-protocol analysis will be conducted. Primary outcomes will be based on the per-protocol analysis, with the intention-to-treat analysis analysis conducted to assess robustness of the results. The measurement data will be expressed as mean ± standard deviation, and the counting data will be expressed as percentage, will be tested by a t test and chi-square test respectively. All statistical tests will be 2-sided and *P* values less than .05 will be considered to be statistically significant.

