### Sample size

2.3

The sample size was calculated based on the total clinical effective rate at 12 weeks. According to the previous literature,^[24]^ we hypothesized that the total clinical effective rate of the blank control group and LPGBD group at 12 weeks will be 73% and 93%, respectively. Set a=0.25 (2-sided) and b = 0.10. We use PASS 15 software (PASS 15.0.5 NCSs, LLC, USA) to calculate the size of the blank control group and LPGBD group N1 = N2 = 41. Assuming that 20% of patients may be lost during follow-up, a total of 100 patients will be recruited.

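### The primary analysis is per-protocol, with intention-to-treat only as a robustness check, in what is in substance a superiority trial; the headline result can therefore be biased, plausibly but not certainly toward LPGBD

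*Protocol article*

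**What the plan says.** Section 9 of the protocol article announces both an intention-to-treat and a per-protocol analysis and then ranks them: "Primary outcomes will be based on the per-protocol analysis, with the intention-to-treat analysis analysis conducted to assess robustness of the results". It gives no reason for the ranking. The same section adds: "All statistical tests will be 2-sided and *P* values less than .05 will be considered to be statistically significant".

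Five other places bear on what this choice means here.

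- **Sample size (2.3)** plans on effective rates of 73% (control) and 93% (LPGBD) at 12 weeks and allows for attrition: "Assuming that 20% of patients may be lost during follow-up". No non-inferiority margin or objective appears anywhere.
- **Blinding (2.5)** says "Due to the nature of TCM, doctors and patients will know the grouping information", but also that "principal investigator, statisticians, and outcome evaluators will be blinded to group allocation".
- **Exclusion criteria (2.2), item 9** lists, among the reasons for exclusion, not using the drugs as prescribed, an effect that cannot be judged, and incomplete data.
- **Patient safety (2.8)** names rash, skin allergy and liver or kidney damage as possible events with TCM and says "Clinicians record the occurrence of any adverse events and the intervention will be stopped immediately".
- **Discussion (10)** describes dropout as high and likely to affect the results, and calls the scale self-rated.

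**The concern.** The question is whether adding LPGBD gives a higher effective rate than conventional treatment alone. In a superiority comparison, the analysis of all patients as randomised is the one whose validity rests on the randomisation. A per-protocol set is chosen afterwards, by adherence, tolerability and completeness of data. Those can depend on the arm and on how the patient is doing.

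Three features make this more than a formality here. Patients and treating doctors, who largely determine adherence and withdrawal, know the arm. The grounds in exclusion item 9 cannot be known at entry. Only one arm has the extra burden of a twice-daily decoction for 12 weeks on top of the shared drugs. If patients who do poorly or tolerate treatment poorly drop out of one arm's denominator, that arm's effective rate rises with no true effect. If the two analyses disagree, section 9 makes the per-protocol result the trial's answer.

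**Working it through.** **Inputs from the article.** Rates of 73% and 93%; planning alpha 0.25 two-sided and beta 0.10; 41 per arm; 20% loss; 100 patients at 1:1, so 50 per arm; test at two-sided 0.05.

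**The plan's own figure.** For two proportions with pooled variance and no continuity correction,

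n = [z(1−α/2)·√(2·p̄(1−p̄)) + z(1−β)·√(p₁(1−p₁)+p₂(1−p₂))]² / (p₂−p₁)².

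With p̄ = 0.83, z = 1.150 and 1.282, this gives 40.2, rounded up to 41 per arm, as stated. 41 × 1.2 = 49.2, rounded up to 50 per arm, or 100 in total, also as stated. (The planning alpha of 0.25 conflicts with the 0.05 test in section 9. That is a separate matter, but it affects the power statement below.)

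**Effect of exclusions when there is no true effect.** These are assumptions, since the article gives no arm-specific exclusion figures: the true rate is 73% in both arms, control exclusions are random, a share d of LPGBD patients is excluded, and a share r of those excluded would have responded. The LPGBD per-protocol rate is then

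(0.73 − d·r) / (1 − d).

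The false-positive rate is the exact binomial probability that the uncorrected chi-square test rejects at 0.05.

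| LPGBD excluded (d) | Responders among them (r) | LPGBD rate | Patients, control vs LPGBD | False-positive rate |
|---|---|---|---|---|
| 20% | 73% (random) | 73.0% | 40 vs 40 | about 5% |
| 20% | 60% | 76.3% | 40 vs 40 | about 6% |
| 20% | 50% | 78.8% | 45 vs 40 | 9.2% |
| 20% | 40% | 81.3% | 45 vs 40 | 14.4% |
| 25% | 40% | 84.0% | 42 vs 38 | 21.7% |
| 25% | 30% | 87.3% | 42 vs 38 | 35.6% |

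For example, (0.73 − 0.20 × 0.40)/0.80 = 0.65/0.80 = 0.8125. The fourth row assumes 10% random exclusion in control; with 20% in both arms (40 vs 40) it is 14.2%, so unequal dropout is not needed. In the fifth row the spurious difference is 84 − 73 = 11 points, over half of the planned 20.

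**Extreme and mirror cases** (normal approximation, 50 randomised per arm). If 20% of LPGBD patients are excluded and all are non-responders, with 20% random exclusion in control, the LPGBD rate is 0.73/0.80 = 91.2%. The difference is +18.2 points and the chance of a significant result favouring LPGBD is 57%. If the selective loss is in control instead, the difference is −18.2 points, with a 57% chance of a significant result against LPGBD. If only non-responders are excluded, equally in both arms, the difference is 0 and the rejection rate stays at 5%.

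**Power with intention-to-treat as primary** (two-sided 0.05).

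- 50 per arm with complete outcomes, 73% vs 93%: 76.7%.
- 41 per arm, 73% vs 93% (the evaluable number planned): 68.0%.
- 50 per arm, 20% missing in each arm counted as ineffective: 0.73 × 0.8 = 58.4%, 0.93 × 0.8 = 74.4%, power about 39%.

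**The case against.** The tempting stronger reading is that the result *is* biased toward LPGBD. The documents do not support that. They give one 20% loss figure for the whole trial and say nothing about who will be excluded or from which arm. Control patients who know that they receive only conventional treatment could leave for lack of effect, which would push the result against LPGBD. Every selective scenario in the table places the selection in the LPGBD arm by assumption. This objection stands in full and limits the claim to a possible bias with a plausible direction.

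A reader might also infer from section 2.8 that LPGBD patients with an adverse event automatically leave the primary analysis. That section stops the intervention; it does not end follow-up or define the per-protocol set, and its wording covers both arms. Exclusion item 9 makes such removal likely, but it remains an inference.

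The stated blinding of outcome evaluators and statisticians should limit knowingly selective exclusion at the analysis stage. It does not prevent differential withdrawal or non-adherence by unblinded patients and doctors, so it softens the point without removing it.

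The intention-to-treat analysis is pre-specified, so a discrepancy would be visible. But section 9 also settles which analysis would prevail.

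Finally, counting missing outcomes as ineffective is not neutral. With 25% missing in LPGBD and 15% in control, all at random and with no true effect, the rates become 0.73 × 0.75 = 54.8% and 0.73 × 0.85 = 62.1%. That is a spurious 7 points against LPGBD, with about 12% rejection. This stands and shapes the fix.

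**Conclusion.** The concern holds as a defect in a choice that section 9 states outright; it is not a detail left to an analysis plan. With no margin and a 73% versus 93% hypothesis, the usual reason for giving a per-protocol analysis weight is absent, and the primary conclusion depends on exclusions made after randomisation in a trial where patients and doctors know the arm.

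The size cannot be read from the documents. Under the stated assumptions the false-positive rate runs from about 5% (random exclusion) through about 14% to about 36%. The sign reverses if the selective loss falls in control. Bias toward LPGBD is plausible because of the added decoction, but it is not established. An unpredictable bias is still enough to require the change, because it bears on the headline result.

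**What to change.** In section 9, make the primary analysis of the week-12 total effective rate intention-to-treat, with all randomised patients in their allocated arm, and make per-protocol supportive. Three additions are needed.

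1. State a rule for missing week-12 outcomes. Multiple imputation from the week 4 and week 8 scores already scheduled in section 4.2, with missing-as-ineffective as the sensitivity analysis, is a reasonable choice; the reverse order is also defensible. Both should be reported, because the second is sensitive to unequal dropout.
2. Define the per-protocol set on its own, and say that the post-randomisation grounds in exclusion item 9 do not remove anyone from the intention-to-treat set.
3. State that patients whose intervention has stopped keep their planned week 4, 8 and 12 assessments. This leaves the stopping rule itself untouched.

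The text change is short and the visits already exist. The real cost is power: the effect may be diluted and the stated power must be recalculated. With 20% missing per arm counted as ineffective, power is about 39% at 50 per arm. Not all of the gap from 90% is due to the fix: at two-sided 0.05, the planned 41 evaluable per arm give only 68% even at the full 73% versus 93%. The shortfall should be dealt with in the sample size, not by keeping per-protocol as primary.

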**Methods::**

In this randomized controlled trial, a total of 100 eligible patients will be allocated to the blank control group or LPGBD group in a ratio of 1:1. The treatment period was 12 weeks. The primary outcome measure will be the total clinical effective rate. The Secondary outcomes will include IBS clinical symptom scores, IBS-Severity Scoring System, IBS-Quality of life, Hamilton Rating Scale for Anxiety, Hamilton Rating Scale for Depression, and Bristol Stool Form Scale. The safety outcome will include Echocardiogram, blood examination (including blood routine test, liver function test, and renal function test), urine routine test and stool routine test. The evaluation indicators and all safety results will be performed at baseline, week 4, week 8 and week 12.

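### Section 9 names only a t test for secondary scales measured at baseline and three later visits; adjusting for baseline would make these secondary results more precise without new data

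*Protocol article*

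**What the plan says.** Section 9 (Statistical analysis) covers continuous data in one sentence. On presentation: "The measurement data will be expressed as mean ± standard deviation". On testing, continuous and count data "will be tested by a t test and chi-square test respectively". The level is two-sided 0.05. Neither that section nor any other names a covariate, a mixed model, a repeated-measures analysis of variance or generalised estimating equations.

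The schedule is equally explicit. The abstract's Methods paragraph says "The evaluation indicators and all safety results will be performed at baseline, week 4, week 8 and week 12". Section 4.2 repeats it scale by scale, for example "IBS-SSS will be measured on week 0, 4,8, 12", "IBS-QOL will be measured on week 0, 4,8, 12" and "HAMA will be measured on week 0, 4,8, 12". The symptom scores, the Hamilton depression scale and the Bristol stool form scale follow the same four visits.

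The primary outcome (section 4.1) is the total effective rate at week 12. It is binary and goes to the chi-square test.

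**The concern.** The trial collects a baseline value and three follow-up values on every secondary scale, then names a test that takes no covariate and does not model the correlation between a patient's visits. Symptom, quality-of-life and mood scores usually track within a patient, so part of the spread at week 12 can be predicted from baseline. A t test on week-12 scores leaves that spread in the error term. A t test on changes removes some of it but adds the noise of the baseline measurement.

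What is at stake is the width of the confidence intervals, and the power, for the secondary comparisons. This matters in a trial of this size: 100 recruited with 20% loss assumed (section 2.3) leaves 100 × 0.80 = 80 patients, or 40 per arm. In addition, section 9 does not say which visit carries the result for each scale.

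**Working it through.** **The plan's own figure.** Section 2.3 gives 41 per arm for 73% against 93%: "Set a=0.25 (2-sided) and b = 0.10". With the pooled two-proportion formula, p̄ = 0.83:

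n = [1.150 × √(2 × 0.83 × 0.17) + 1.282 × √(0.73 × 0.27 + 0.93 × 0.07)]² / 0.20² = (0.611 + 0.656)² / 0.04 ≈ 40.2, so 41.

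The figure reproduces from the stated inputs, but it concerns the binary primary outcome and does not bear on this point. (The 0.25 there against 0.05 in section 9 is a separate matter.) No SD, effect or sample size is stated for any continuous scale, so the loss can only be shown over a range.

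**Inputs.**
- Patients analysed: 40 per arm, as above.
- Test level: 0.05 two-sided (section 9).
- r, the correlation between baseline and week-12 score: not in the document; assumed 0.3, 0.5, 0.7, with 0 as the limiting case.
- True difference for the power illustration: 0.5 SD, also assumed.

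**Variance of the week-12 treatment difference, relative to a t test on raw week-12 scores** (equal SDs at baseline and week 12; the single degree of freedom spent on the covariate ignored):
- t test on raw scores: 1
- t test on change from baseline: 2(1 − r)
- ANCOVA on the week-12 score with baseline as covariate: 1 − r²

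ANCOVA is never worse than the raw-score test, because 1 − r² ≤ 1. It is never worse than the change-score test, because 2(1 − r) − (1 − r²) = (1 − r)² ≥ 0.

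**Power at 0.5 SD**, as Φ(0.5 / SE − 1.96), with SE = √(2/40) × √(variance factor):
- Raw-score t test: SE = 0.2236; 0.5/0.2236 − 1.96 = 0.276; power 0.61.
- ANCOVA at r = 0.5: SE = 0.2236 × √0.75 = 0.1936; 0.5/0.1936 − 1.96 = 0.622; power 0.73.

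| Assumed r | Change-score factor | ANCOVA factor | ANCOVA power (raw t test 0.61) | 40 per arm with ANCOVA equals, with raw t test |
|---|---|---|---|---|
| 0 | 2.0 | 1.00 | 0.61 | 40 |
| 0.3 | 1.4 | 0.91 | 0.65 | 40/0.91 = 44 |
| 0.5 | 1.0 | 0.75 | 0.73 | 40/0.75 = 53 |
| 0.7 | 0.6 | 0.51 | 0.88 | 40/0.51 = 78 |

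Below r = 0.5 the change-score test is worse than the raw-score test. Above it the change-score test is better, but it still trails ANCOVA.

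**The case against.** **The article is condensed, and covariates belong in the analysis plan.** Silence on covariates would be no finding. But the article is not silent: it names the test for continuous data. If a fuller plan adjusts for baseline, section 9 misdescribes it and still needs the change of wording.

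**The t test is valid.** This stands. Under randomisation an unadjusted comparison is unbiased, and its type I error already allows for chance differences at baseline. A reader might infer that unadjusted tests leave the results open to bias from baseline imbalance. The probability of an imbalance of a given size is not an error rate, and the document does not support that reading.

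**The text does not say what is tested.** This also stands. Section 9 does not state whether raw scores or changes are compared, or at which visits, and the word unadjusted is an inference from the test named. So it cannot be said that baseline is thrown away: a change-score test would use it. The point survives because ANCOVA is at least as precise as either version.

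**Stronger readings to avoid.**
- That patients with a missing visit are dropped. Section 9 plans both intention-to-treat and per-protocol analyses and does not say how missing visits enter, so this would rest on silence.
- That six scales at three visits make 18 tests with a badly inflated false-positive rate. Visit-by-visit testing is not stated, the scales and visits would be correlated, so a calculation for independent tests would overstate the risk, and no claim is tied to any secondary test.
- That the main result is affected. The primary outcome is binary, and nothing here shows that its analysis needs a covariate.

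**The gain is uncertain.** True: r is unknown, and at r = 0 ANCOVA gains nothing over the raw-score test. Hence a range and not one figure.

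**Conclusion.** The point holds as a matter of efficiency in the secondary outcomes. A t test is the only method section 9 names for scales with a baseline and three follow-up visits, and on either reading it is less precise than adjusting for the baseline score. Against a raw-score t test, ANCOVA cuts the variance by 9%, 25% or 49% at r of 0.3, 0.5 or 0.7. At r = 0.5 and a 0.5 SD difference, power with 40 per arm goes from about 61% to 73%. Both r and the effect size are assumptions, and equal SDs at the two visits are assumed.

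It is not a bias and does not touch the primary outcome or its sample size. It is worth correcting because the data are already being collected and the remedy is cheap.

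**What to change.** In section 9, for the repeatedly measured secondary scales, replace the t test with one of the following, in all randomised patients with data:
- ANCOVA of the week-12 score on arm, adjusted for the baseline score; or
- a mixed model for repeated measures with arm, visit, arm-by-visit and baseline score. This also uses the week-4 and week-8 values of patients without a week-12 score.

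State that the week-12 difference between arms, with its 95% CI, is the single main comparison for each scale, and that weeks 4 and 8 are supportive.

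Treat the ordinal items separately. The three symptom grades (0, 2, 4, 6) can be analysed as a summed score or with an ordinal model. The Bristol scale calls for an ordinal model. In each case adjust for baseline.

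The cost is a change of wording, best made before the data are unblinded, and a little more analysis work. The analyses can be run in SPSS, the package section 9 already names. No new data, visits or patients are needed.

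### The chi-square test planned for the primary outcome is valid but uses no baseline information; adjusting for week-0 IBS-SSS may gain some power without extra patients.

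*Protocol article*

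**What the plan says.** Primary outcome (4.1) makes the endpoint binary: "The main outcome will be the total clinical effective rate of the 2 groups after treatment (week 12"), where cure, significant effect and effective count as success and ineffective as failure. It does not say how the four grades are derived.

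Statistical analysis (9) names one test for each type of data. Measurement data and count data "will be tested by a t test and chi-square test respectively", and the per-protocol set is primary. No covariate, stratified or adjusted analysis is mentioned.

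Secondary outcomes (4.2) collects baseline severity in any case: "IBS-SSS will be measured on week 0, 4,8, 12". The symptom scores follow the same schedule. Randomization (2.4) has patients "randomly assigned to blank control group and LPGBD group in the ratio of 1:1" and mentions no stratification by severity.

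**The concern.** The named primary test uses only the two success proportions. A covariate measured before treatment that predicts the outcome can sharpen the treatment comparison, and here a candidate is already collected. If week-0 severity is prognostic, the chi-square test leaves that information unused. In a trial of 100 patients, a few points of power gained without recruiting anyone are worth having. They come at the price of one pre-specified model in place of one simple test.

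**Working it through.** **Inputs.** Rates: "at 12 weeks will be 73% and 93%, respectively" (control, LPGBD). Design error rates: "Set a=0.25 (2-sided) and b = 0.10". Analysis threshold: two-sided, P "values less than .05 will be considered to be statistically significant". Loss: "Assuming that 20% of patients may be lost during follow-up, a total of 100 patients will be recruited". That is 50 per arm, or 50 × 0.8 = 40 evaluable per arm.

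**1. The plan's own figure.** Pooled-variance formula without continuity correction:

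n = [z(1-α/2)·√(2p̄q̄) + z(1-β)·√(p1q1 + p2q2)]² / (p2 - p1)²

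Here p̄ = 0.83, √(2 × 0.83 × 0.17) = 0.531 and √(0.73 × 0.27 + 0.93 × 0.07) = 0.512.

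- α = 0.25: (1.150 × 0.531 + 1.282 × 0.512)² / 0.04 ≈ 40.2, so 41 per arm. The stated 41 is reproduced.
- α = 0.05: (1.960 × 0.531 + 1.282 × 0.512)² / 0.04 ≈ 72.0, so 73 per arm.

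**2. Power of the unadjusted test at 0.05.** Φ[(0.2√n - 1.960 × 0.531) / 0.512] gives 67% at n = 40, 68% at 41 and 77% at 50. Simulation at n = 40 gives about 70%.

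**3. What adjustment adds.** The article does not say how strongly week-0 IBS-SSS predicts the outcome, so a range is assumed. Model: a latent normal response cut at 73% and 93%, correlated r with baseline, 40 per arm, two-sided 0.05, 10,000 runs. The last column repeats the comparison in a separate simulation.

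| r | Chi-square | Adjusted score test | Change | Repeat simulation |
|---|---|---|---|---|
| 0 | 70.1% | 69.2% | -0.9 | 70% → 69% |
| 0.3 | 70.4% | 71.7% | +1.3 | 70% → 71% |
| 0.5 | 69.7% | 75.0% | +5.3 | 71% → 75% |
| 0.6 | 70.4% | 78.3% | +7.9 | 69% → 77% |

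The Monte Carlo standard error of one power figure is √(0.7 × 0.3 / 10,000) ≈ 0.5 points, so the changes at r = 0 and 0.3 are small.

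**4. Cross-check with another model and test.** A logistic outcome model with a likelihood-ratio test (4,000 runs) was run against R², the share of control-arm outcome variance explained by baseline.

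- 40 per arm: about +1 point at R² = 0, +2 at 0.05, +4 at 0.10 and +7 at 0.18.
- 50 per arm: 0, +1, +3 and +5 points.

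The two scales can be linked. For a latent normal cut at 73%, R² = r²·φ(0.613)²/(0.73 × 0.27) = r² × 0.331²/0.197 ≈ 0.555r². So r = 0.3, 0.5 and 0.6 correspond to R² of about 0.05, 0.14 and 0.20, and the two sets of results agree.

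**5. Type I error.** With 83% in both arms: chi-square 5.1 to 5.4%, adjusted score test 5.3 to 5.7%, penalised standardised risk difference 5.5 to 5.8%. The likelihood-ratio test with 73% in both arms gave 5.0 to 5.5% at 40 per arm.

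**6. Sparse failures.** Expected failures are 40 × 0.27 = 10.8 in control and 40 × 0.07 = 2.8 under LPGBD, 13.6 in all. The chance of none under LPGBD is 0.93^40 ≈ 5.5%, about 1 trial in 18. The ordinary maximum-likelihood treatment coefficient then does not exist.

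**7. Can adjustment restore 90% power?** As a rough guide, n(1 - R²) takes 73 per arm to 73 × 0.95 = 69.4, 73 × 0.90 = 65.7 and 73 × 0.82 = 59.9, that is 70, 66 and 60. All exceed the 50 per arm recruited.

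**The case against.** The strongest reply is that nothing here is wrong. A chi-square test is valid for a randomised comparison of two proportions, and its error rate already allows for chance baseline imbalance. Covariate choice is often settled in an analysis plan, and none is shown. The validity point stands in full. The second point stands only in part, because the article does not leave the primary test open: it names one.

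The reply also says that the benefit is conditional. This stands. The article does not say how the effective categories are graded. If they reflect change from baseline, neither the strength nor the direction of the association can be inferred.

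Two technical points stand as well. With fewer than 3 failures expected under LPGBD, an ordinary logistic fit can fail, so the fix must name a penalised one. The adjusted test is also slightly liberal: matching its size to that of the chi-square test cut the gain at r = 0.6 from about 8 points to 6.

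A reader might infer two stronger claims that the document does not support:

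- **That the trial definitely loses power.** This would need a known association between week-0 IBS-SSS and the effective rate, and none is given.
- **That adjustment would cure the low power.** The 67 to 70% comes from sizing at alpha 0.25 and testing at 0.05. That is a separate conflict, and it remains after adjustment (step 7).

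**Conclusion.** The point holds as a conditional efficiency improvement and is minor. The planned test is valid, and adjustment would improve precision rather than remove a bias. At 40 per arm, 73% v 93% and two-sided 0.05, the change in power is about -1 point at correlation 0, +1 to 2 at 0.3, +4 to 5 at 0.5 and +8 at 0.6. Formula power rises by about one point per added patient per arm (67% at 40, 77% at 50), so the gain at 0.5 is worth roughly 4 to 5 patients per arm.

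These figures rest on the assumed correlations, on the article's own rates and 20% loss, and on a single covariate. The worst case in the range is small, which is why the change is still worth offering.

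**What to change.** Before unblinding, state in Statistical analysis that:

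1. The primary test is the score test for treatment from a logistic model with treatment and week-0 IBS-SSS as the single covariate.
2. The effect is reported as a standardised risk difference from a penalised (Firth) logistic fit with a bootstrap 95% CI, so that an estimate exists even if the LPGBD arm has no failures.
3. The unadjusted chi-square test and raw risk difference are kept as a sensitivity analysis.

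Blinding (2.5) keeps the statisticians unaware of allocation, so the choice can be made without sight of results by arm.

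No new data, visits or patients are needed. The cost is about 1 point of power if baseline is not prognostic, type I error of up to about 5.7% for the test and 5.8% for the standardised difference, and a somewhat more complex analysis. The team should confirm that the named software, SPSS 22.0, can run the penalised fit and bootstrap, or name another package. The two alpha values must be reconciled separately.
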